| Outcome measures               | Primary and secondary outcomes as per BICS.                                                                                                                                                                                                                                                                                                                                                                                                                                                                                                                                                                                                                                                                                                                                                                                                                                                                                                                                                                                                                                                                                                                                                                                                                                                                                                                                                                                                                                                                                                                                                                                                                                                                      |

|                     |                                                                                                                         |
|---------------------|-------------------------------------------------------------------------------------------------------------------------|
|                     | The sub-study outcome measures will be NT-proBNP, hs-TnI, hs-CRP, Galectin and echocardiography parameters.             |
| Statistical methods | Participants will be risk stratified for occult heart disease and analysed as sub-groups within the main BICS analysis. |

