| Sub-study assessment           | 
Participants will be invited to take part in the BICS sub-study after they have agreed to take part in the main BICS study. This may be during their BICS recruitment visit or during the titration period. Those who agree will be invited to:
 
 
undergo echocardiography after commencing study medication (within 12 weeks of randomisation).
 
provide a blood sample for measurement of NT-proBNP, hs-TnI, hs-CRP and Galectin soon after commencing study medication (within 12 weeks of randomisation) and at the end of the study treatment period.
 
 
Baseline blood sampling and echocardiography should not be performed within 4 weeks of recovery from an exacerbation of COPD. If the participant experiences prolonged period(s) of exacerbation before starting study medication or during titration, the 12 week window can be extended to permit the participant to take part in the sub-study. If the participant has an exacerbation when the blood/echocardiography are due, the 12 week window can be extended to permit the participant to take part in the sub-study. The 12 month bloods will be taken at 12 month visit (if face-to-face) or during the down-titration of the study medication.
 
Note: if sites are unable to offer echocardiography, they can undertake the blood component of the cardiac sub-study. This will be explained to potential participants when they are invited to take part in the cardiac sub-study. If echocardiography becomes available at the site before the participants complete their follow-up within BICS, a late echocardiography could be offered to participants.
 |

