## SUB-STUDY DESIGN

Participants in BICS will adhere to the main BICS study protocol. Within the sub-study, a limited number of additional investigations will be performed during BICS assessment visits to risk stratify participants for occult undiagnosed heart disease.

Participants enrolled into BICS in sites that have agreed to participate in the sub-study and who have agreed to be contacted about further studies, will be invited to take part in the sub-study after they have agreed to take part in the main BICS study. This may be during their BICS recruitment visit or during the dose titration phase. After providing written informed consent participants will undergo echocardiography at a mutually convenient time, ideally during one of the dose titration assessments, but up to 12 weeks following randomisation is acceptable (and can be delayed if the participant exacerbates during this period). Participants will also be invited to provide two 15ml blood samples, one ideally during the dose titration phase, but up to 12 weeks following randomisation is acceptable (and can be delayed if the participant exacerbates during this period) and one at the final assessment visit at the 12 month visit (if face-to-face) or during the down-titration of the study medication.

Note: if sites are unable to offer echocardiography, they can undertake the blood component of the cardiac sub-study. This will be explained to potential participants when they are invited to take part in the cardiac sub-study. If echocardiography becomes available at the site before the participants complete their follow-up within BICS, a late echocardiography could be offered to participants.

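### The cardiac sub-study sorts participants into high- and low-risk subgroups using blood and echo measurements taken after study drug has started, so randomisation does not fully protect the within-subgroup comparison

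*Protocol*

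**What the plan says.** All of this is in Appendix 6 (BICS Heart Study).

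- **Echo timing.** In the Synopsis, participants "undergo echocardiography after commencing study medication (within 12 weeks of randomisation". Sub-study Design places the scan "ideally during one of the dose titration assessments, but up to 12 weeks following randomisation is acceptable".
- **Blood timing.** There are two samples: "soon after commencing study medication (within 12 weeks of randomisation) and at the end of the study treatment period". The Synopsis calls the first round of blood and echo baseline.
- **Extensions.** After exacerbations, "the 12 week window can be extended to permit the participant to take part in the sub-study", with no upper limit given. Sub-study Design agrees: "up to 12 weeks following randomisation is acceptable (and can be delayed if the participant exacerbates during this period".
- **Late scans.** Where a site gains echocardiography before a participant finishes follow-up, "a late echocardiography could be offered to participants".
- **Use as classifier.** Proposed Analyses applies cut-offs on troponin, ejection fraction, NT-proBNP, diastolic function, atrial volume and ventricular mass to sort participants into high and low risk. It then compares bisoprolol with placebo in each class by negative binomial regression. This serves the sub-study's primary objective, which is whether any benefit is confined to the high-risk class.
- **Use as outcome.** "The sub-study outcome measures will be NT-proBNP, hs-TnI, hs-CRP, Galectin and echocardiography parameters".

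No sample or scan before the first dose is required. The sections on blood assays and echocardiography count 12 weeks from randomisation. The Synopsis adds that the drug has already been started.

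**The concern.** A subgroup supports a randomised comparison when membership is fixed before treatment can influence it. Here membership depends on values measured on bisoprolol or placebo. If bisoprolol moves people across a cut-off, the high-risk class on bisoprolol and the high-risk class on placebo are different kinds of patient, and part of the difference between them is selection. Blinding and a larger sample do not remove this.

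The protocol makes some movement plausible. Section 2.1 cites a trial in which bisoprolol lowered heart rate, Section 2 cites anti-inflammatory properties of beta-blockers, and the Synopsis lists the classifying measures among the sub-study outcomes. Under Section 8.6 titration takes four to seven weeks, so a measurement near 12 weeks would usually be made on an established dose.

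Timing also depends on the primary outcome. Exacerbations postpone the measurement and, under Section 8.7.1, change the dose during titration. If the drug works, time and dose at measurement could differ between arms.

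At stake is the answer to the sub-study's primary objective, not the main trial result.

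**Working it through.** **1. The plan's own power figures.** Inputs from Appendix 6, Sample size: 900 participants, 10% stopping drug (810 left, 405 per arm), mean 2.22, SD 1.86. Two-sided 5% and 1:1 allocation are taken from the main protocol.

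Power = Φ(difference / (1.86 × √(2/n)) − 1.96), with n = 405 × high-risk share.

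| High-risk share | n per arm | Difference | Power |
|---|---|---|---|
| 50% | 202.5 | 0.52 | 80.3% |
| 40% | 162 | 0.58 | 80.1% |
| 30% | 121.5 | 0.67 | 80.2% |
| 20% | 81 | 0.82 | 80.1% |

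The stated 80% reproduces. It assumes the same high-risk share in both arms, which classification after dosing does not guarantee.

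**2. Illustration of the bias.** The marker shift and the correlation are assumptions, because the documents give neither.

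- Between-patient variation follows from 2.22 (1.86): k = (1.86² − 2.22)/2.22² = 1.2396/4.9284 = 0.2515. Frailty is gamma with mean 1 and variance k.
- The marker is standard normal, with correlation 0 or 0.4 with standardised log frailty. High risk means above c, where c gives the stated share on placebo.
- Bisoprolol lowers the marker by s = 0.3 or 0.5 SD before it is measured, so a bisoprolol participant is classed high only if the undisturbed value exceeds c + s.
- Rate ratio in the high class under no effect = E(frailty | marker > c + s) / E(frailty | marker > c), and likewise for the low class.
- Alternative: a true rate ratio of 0.77 (1.70/2.22) in the truly high-risk and 1 in the rest.

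One row by hand (share 50%, s = 0.3, correlation 0): the share classed high on bisoprolol is Φ(−0.3) = 0.382. Of the 0.618 classed low, 0.118 are truly high-risk, which is 0.118/0.5 = 24% of the truly high-risk. Low-class rate ratio = (0.500 + 0.118 × 0.77)/0.618 = 0.956.

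| Share | s | Corr. | Classed high on bisoprolol | No effect: high / low | True 0.77 in high only: high / low |
|---|---|---|---|---|---|
| 50% | 0.3 | 0 | 38% | 1.000 / 1.000 | 0.770 / 0.956 |
| 50% | 0.5 | 0 | 31% | 1.000 / 1.000 | 0.770 / 0.936 |
| 20% | 0.3 | 0 | 13% | 1.000 / 1.000 | 0.770 / 0.981 |
| 20% | 0.5 | 0 | 9% | 1.000 / 1.000 | 0.770 / 0.972 |
| 50% | 0.3 | 0.4 | 38% | 1.033 / 1.040 | 0.796 / 0.987 |
| 50% | 0.5 | 0.4 | 31% | 1.057 / 1.064 | 0.814 / 0.985 |
| 20% | 0.3 | 0.4 | 13% | 1.037 / 1.023 | 0.799 / 0.998 |
| 20% | 0.5 | 0.4 | 9% | 1.063 / 1.035 | 0.818 / 0.999 |

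**3. Either direction of shift.** A simpler model makes the log rate linear in the pre-treatment marker, with an assumed slope of 0.1 to 0.3 per SD and a shift of −0.3 to +0.3 SD. The high-class rate ratio under no effect then runs from about 0.94 (upward shift) to 1.07 (downward shift). Nominal power runs from about 70% to 86%, because the high class shrinks or grows on bisoprolol.

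**4. Against sampling error.** With a 50% share, SE of the high-class log rate ratio under no effect = √[(1/2.22 + 0.2515)(1/202.5 + 1/n₁)].

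- n₁ = 202.5: √(0.7020 × 2/202.5) = 0.083.
- n₁ = 405 × 0.382 = 154.7: 0.089.

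A bias of log(1.033) ≈ 0.033 is about 0.4 SE. Two-sided rejection under no effect rises from 5% to about 6.6%.

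**The case against.** The strongest reply is that no effect of bisoprolol on NT-proBNP, troponin or echo parameters is documented anywhere, so a reader who infers that the subgroups are in fact altered by treatment goes beyond the text. That stands: the supportable statement is that they can be.

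A reader might also infer that the design would manufacture a finding of restricted benefit. The figures do not support this. Under no effect both classes are biased in the same direction. The high-to-low ratio of rate ratios is 0.99 at a 50% share (1.033/1.040) and 1.01 to 1.03 at 20% (1.037/1.023 and 1.063/1.035). When benefit really is confined to the high class, the pattern survives, somewhat diluted.

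Further points have force:

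- The plan's rule is not a single cut-off. For preserved ejection fraction it accepts either NT-proBNP or structural and diastolic criteria, so someone meeting several is not reclassified when one marker moves. The 24% reclassification does not carry over directly.
- Twelve weeks is the outer bound, and measurement during titration is preferred. An exacerbation does not simply mean longer exposure, because Section 8.7.1 reduces or interrupts the drug. Waiting until four weeks after recovery sensibly avoids measurement in acute illness.
- No passage says that late echoes will define subgroups, and the statistical analysis plan, not shown, may deal with them.
- Reading samples and scans only after the participant's 12 months limits assessor bias.

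None of this restores a baseline subgroup. Delayed reading does not undo a drug effect already present in the sample or image, and an analysis plan cannot supply a pre-dose value that was never collected.

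**Conclusion.** The concern holds as a structural weakness of the sub-study. Its classes rest on measurements made after study drug has started, which are also listed as outcomes and whose timing depends on exacerbations, so the within-class comparison is not fully randomised. This needs no effect size.

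The likely size looks modest. With a downward shift of 0.3 to 0.5 SD and a correlation of 0 to 0.4, the bias in each class is about 0 to 6% under no effect. A true 0.77 confined to the high class becomes about 0.77 to 0.82, with the low class at about 0.94 to 1.00. All of this rests on an assumed shift, an assumed correlation and a simplified single-marker rule.

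It would be wrong to infer damage to the main trial: the overall bisoprolol–placebo comparison does not use these measurements. Should-fix for the sub-study.

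**What to change.** **Remaining recruits.**
- Take the classifying blood sample after sub-study consent and before the first dose. Appendix 6 (Synopsis, Ethical Considerations) already allows the approach at the recruitment visit, and Sections 7.3 and 8.4 have the drug couriered to the home afterwards. The Identification of Participants paragraph, which mentions only the titration phase, should be aligned.
- Do the echo before the first dose only where it can be booked without delaying treatment.
- Define subgroups from pre-dose values wherever they exist, and exclude late echoes from subgroup definition.

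**Participants measured after dosing.**
- Keep them in the analysis, but label subgroup results based on post-dose values as exploratory.
- Report marker distributions and the high-risk share by arm.
- Add a sensitivity analysis by time from first dose to measurement.

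**Cost.** Excluding late echoes and adding the reporting cost little. Moving the blood sample means some rescheduling. Pre-dose data will be incomplete, especially with remote recruitment, where sub-study visits are extra face-to-face visits. Appendix 8 reports 429 participants recruited before the pause. How many joined the sub-study is not stated, so the amount of post-dose data is unknown. The sub-study will have to make a weaker claim. Moving everyone already measured into a sensitivity analysis, or requiring a pre-dose echo from all, would cost more than a bias of this size warrants.

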## 7.6 Trial assessments

After obtaining written informed consent, participants will be assessed as follows:

- At the recruitment visit; face to face or via telephone/video call
- At 1 week, face to face\* (dose titration)
- At 2 weeks, face to face\* (dose titration)
- At 3 weeks, face to face\* (dose titration)
- At 4 weeks, face to face\* (dose titration)
- At 6 months (26 weeks); face to face\*
- At 12 months (52 weeks); face to face\*
- 1 week after cessation of study medication by telephone
- Post study; examination of hospital and GP records to obtain primary outcome data.

\* Whilst the COVID-19 pandemic is ongoing, the recruitment visit can be done as face-to-face, with appropriate precautions in place (PPE, social distancing, hand hygiene etc). All other visits (titration, and 6/12 month follow-up) will be conducted remotely, via telephone/video call. Following a remote assessment, if there are clinical concerns, the site can arrange a face-to-face visit with appropriate precautions in place.

In the event that a participant is unable to complete a scheduled assessment because of an acute illness e.g. exacerbation of COPD, the assessment will be appropriately postponed, to be conducted when the participant is stable, ideally within 4 weeks of the scheduled assessment. Similarly, participants who are unable to attend a scheduled assessment for another reason will have this rearranged, ideally within 4 weeks of the scheduled assessment. Participants unable to attend for face to face assessment at six and twelve months can be

followed up by telephone, a home visit, or sent the questionnaire to complete at home. Similarly, recruitment of patients who, for example have limited mobility or who live some distance from the study site, can be carried out during a home visit. During the COVID-19 pandemic, to reduce footfall in hospitals and GP practices, a face-to-face recruitment visit can be done at home, with appropriate COVID-19 measures in place (PPE, social distancing, hand hygiene).

The schedule for data collection within the study is outlined in Table 2 (overleaf).

Potential participants will be informed in the PIL that they can raise any issues with the study team who will arrange further examination if indicated. If the participant or nurse have concerns, these will be discussed with a medically qualified local investigator and suitable arrangements made for the participant to be seen at a later date.

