### **8.7.2 Dose reduction at end of follow-up**

Following completion of the 12 month dosing period participants will be weaned off study drug over the following weeks (3-2-1 tablet(s) od) in order to avoid possible rebound myocardial ischemia. A similar regime will be recommended for participants who wish to discontinue medication during the study.

| Maintenance dosage: | At final visit | Subsequent week |       |      |
|---------------------|----------------|-----------------|-------|------|
|                     |                | 1               | 2     | 3    |
| 1 tab               | Stop           |                 |       |      |
| 2 tab               | 1 tab          | stop            |       |      |
| 3 tab               | 2 tab          | 1 tab           | stop  |      |
| 4 tab               | 3 tab          | 2 tab           | 1 tab | stop |

Successful weaning will be confirmed by the research nurse by telephone one week after anticipated cessation of treatment. Successful weaning is defined as reduction of dose as described above prior to stopping. Any adverse effects experienced during weaning will be documented within the CRF.

Figure 3: Schematic representation of dose titration

[figure not shown]

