## ABSTRACT

The Bisoprolol in COPD Study (BICS) is a pragmatic randomised double-blind placebo-controlled trial investigating the effectiveness of the beta-blocker Bisoprolol in reducing exacerbations in people with Chronic Obstructive Pulmonary Disease (COPD) who do not currently fulfil criteria for beta-blocker use. A cardiac sub-study nested within BICS will test the hypothesis that the beneficial effects of beta-blockers on COPD exacerbations are restricted to COPD patients at high risk of occult, previously undiagnosed heart disease. To do this, in the first 12 weeks during their involvement in BICS, participants recruited in secondary care sites will be invited to participate in the sub-study comprising an echocardiogram at the start of the one year treatment period and blood samples for measurement of biomarkers: N-terminal pro-Brain Natriuretic Peptide (NT-proBNP), high sensitivity Troponin I (hs TnI), high sensitivity C-reactive protein (hs-CRP) and Galectin at the start and end of the one year treatment period. There are no changes to the main BICS protocol. These investigations will be used to further analyse the effects of beta-blockers on COPD exacerbations by risk stratifying participants for heart disease. This sub-study will establish if beta-blocker therapy is beneficial in all COPD patients (via a yet to be established mechanism) or in a sub-group of COPD patients with occult heart disease (via cardiac protection).

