### **Blood assays:**

15 ml blood samples will be taken by a member of the BICS research team at the site:

- 1) Within 12 weeks of randomisation, however, this may be delayed if the participant exacerbates after joining the study
- 2) At the final study assessment (approximately week 52) (if taking study treatment), however this may be delayed by exacerbation.

The 15ml sample will be processed into a serum (plain) tube (10ml) and an EDTA tube (5ml).

The tubes will be centrifuged at 1000-2000g for 10 minutes, and the plasma and serum stored in ~1ml aliquots at -70°C ideally within 1 hour of collection. Samples will be stored locally and sent in batches to Aberdeen. All samples will be stored at -70°C. Samples will be identified by study number and not by the participant's name.

One aliquot per participant per time point will be analysed for N-terminal pro-Brain Natriuretic Peptide (NT-proBNP and Galectin, analysis by [name] in Dundee).

One aliquot per participant per time point will be analysed for high sensitive Troponin I and hs-CRP (hs TnI, analysis by [name] in Edinburgh).

All samples will be analysed in the two core labs mentioned above. Any residual material will be retained in Aberdeen (HRA approved tissue bank - NHS Grampian Biorepository).

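### When the 12-month visit is remote, the cardiac sub-study lets its end-of-treatment blood sample be drawn during weaning, so the four biomarkers would mix full-dose and reduced-dose values

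*Protocol*

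**What the plan says.** Appendix 6 gives several accounts of when the second blood sample is taken.

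- The Abstract places the biomarker samples "at the start and end of the one year treatment period".
- The Synopsis asks for a sample soon after starting study medication "and at the end of the study treatment period". In the same cell it adds: "The 12 month bloods will be taken at 12 month visit (if face-to-face) or during the down-titration of the study medication".
- Sub-study Design repeats the alternative: "one at the final assessment visit at the 12 month visit (if face-to-face) or during the down-titration of the study medication".
- Blood Assays gives "At the final study assessment (approximately week 52", on condition that the participant is still taking study treatment. It allows delay for an exacerbation and does not mention down-titration.
- Participant Withdrawal keeps the timing unchanged for people who have stopped the drug or are fixed on 0 tablets.

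Section 7.6 says of the pandemic period: "All other visits (titration, and 6/12 month follow-up) will be conducted remotely, via telephone/video call". Section 8.6 sets treatment at 12 months, with weaning in the weeks after the week-52 assessment. Section 8.7.2 tabulates the wean and gives its reason as "in order to avoid possible rebound myocardial ischemia".

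On the role of the biomarkers, the Synopsis states: "The sub-study outcome measures will be NT-proBNP, hs-TnI, hs-CRP, Galectin and echocardiography parameters".

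**The concern.** A sample meant to describe participants at the end of a year on treatment may be drawn after the dose has begun to fall. Placebo participants also take fewer tablets in those weeks, but only the bisoprolol arm loses active drug, so randomisation does not balance the change out. Face-to-face 12-month visits would give values on the maintenance dose and remote ones would give values on a reduced dose. Pooling the two makes the 12-month value an undefined mixture of treatment states. Four named outcome measures are exposed to this. Appendix 6 does not ask for the dose at sampling to be recorded with the sample, so the two kinds of value may be hard to separate later.

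**Working it through.** The plan states no figure for this point, so there is none to reproduce. The check compares the sampling time with the weaning table.

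**Step 1: is weaning part of the treatment period?** Section 8.6 fixes treatment at 12 months and puts weaning after the week-52 assessment. Section 8.7.2 likewise starts the wean once the 12-month dosing period is complete. Down-titration therefore lies outside the period that the Abstract and Blood Assays describe, and the statements conflict.

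**Step 2: dose during the wean.** The input is the table in Section 8.7.2. Share of maintenance dose = tablets per day in that week ÷ maintenance tablets per day.

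| Maintenance | Tablets in successive weeks from the final visit | Share of maintenance dose | Mean over the window |
|---|---|---|---|
| 4 tablets | 3, 2, 1, then stop | 75%, 50%, 25% | (0.75 + 0.50 + 0.25)/3 = 50% |
| 3 tablets | 2, 1, then stop | 67%, 33% | (0.67 + 0.33)/2 = 50% |
| 2 tablets | 1, then stop | 50% | 50% |
| 1 tablet | stop at final visit | no window | not defined |

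Nobody sampled inside the window is on the maintenance dose. The 50% means assume sampling spread evenly over the wean, which the protocol does not state. They describe dose and not biomarker effect, because the documents give no dose-response for these biomarkers. For 1-tablet participants with a remote visit, the instruction points to a period that does not exist.

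**Step 3: how many samples?** The documents do not settle this. As an illustration only: Appendix 8 reports 429 participants recruited before the pause. If the target is met, 1,574 − 429 = 1,145 are recruited afterwards, and 1,145/1,574 = 72.7%. Applied to the planned 900 sub-study participants, 0.727 × 900 ≈ 655 samples. The split is a poor proxy, for four reasons:

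- Appendix 7 moved 12-month follow-up to telephone for people already enrolled, so some of the 429 are affected too.
- Section 7.6 limits remote visits to the pandemic, so some later recruits may not be affected.
- The 429 is trial-wide, while the sub-study recruits at secondary care sites.
- Both recruitment targets would have to be met.

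**Step 4: is an extra visit needed to avoid this?** No. Appendix 6 (Risks) and Appendix 8 (item 4) already provide a separate face-to-face visit for bloods around 12 months. Neither places it before the first weaning step.

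**The case against.** The strongest reply is that no written analysis is harmed. Proposed Analyses in Appendix 6 uses biomarkers and echocardiography to classify participants by risk of occult heart disease, then compares exacerbations. It plans no between-arm biomarker comparison at 12 months and names no use of the second sample. The first sample and the echocardiogram are unaffected. This stands, and it limits the point to the second-sample biomarker values. It does not remove the point, because the biomarkers are listed as outcome measures and are deliberately sampled twice.

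The first sample may also be taken up to 12 weeks after randomisation, with study drug already started, so the schedule was never a clean before-and-after contrast. That is true, but a comparison of the arms at 12 months does not depend on the first sample.

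A reader might infer more from the reason given for weaning: that rebound ischaemia would raise troponin or NT-proBNP in the bisoprolol arm and reverse the sign of an effect. The documents do not support this. Section 8.7.2 calls rebound only possible and presents the wean as the precaution against it. Section 7.10 says that the cardiovascular reason for weaning does not apply in this trial, and Appendix 1 accepts immediate stopping on similar grounds. No passage gives a size or direction for any biomarker shift.

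Nor does the text direct that samples be taken off drug. Participants on 2 to 4 tablets are on a reduced dose throughout the wean, and for 1-tablet participants the rule is undefined.

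Finally, the amendment history presents the relaxed sub-study timing as a pragmatic choice. Flexibility is reasonable, but it does not require sampling after the dose has started to fall.

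**Conclusion.** The point holds in a limited form. Appendix 6 contradicts itself on when the second sample is taken and on what treatment status. When the 12-month visit is remote, its wording permits sampling at 25% to 75% of maintenance dose and leaves 1-tablet participants without a rule. Because only the bisoprolol arm loses active drug, a treatment effect on the four biomarkers at 12 months would probably be diluted. That judgement assumes that any such effect weakens as the dose falls. The size and direction of the actual shift cannot be computed from the documents.

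The number affected depends on how many 12-month visits are remote. The figure of about 655 of 900 is an illustration and not an estimate. The sub-study's primary stratification analysis and the main trial's exacerbation outcome are not affected. This should be corrected, but it does not threaten the trial's main conclusion.

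**What to change.** 1. Reconcile the Abstract, Synopsis, Sub-study Design, Blood Assays and Participant Withdrawal sections of Appendix 6, so that they give one sampling time and say how participants on 1 tablet, on 0 tablets or already off drug are handled.
2. Book the face-to-face blood visit already planned in Appendix 6 (Risks) and Appendix 8 (item 4) at or shortly before the 52-week assessment, ahead of the first weaning step. Remove the down-titration alternative. The weaning schedule stays as it is.
3. Record the sampling date and the tablets per day at sampling for every second sample.
4. Keep samples already drawn during weaning. Report any 12-month biomarker comparison with and without them, or by dose status at sampling. Dropping them from the main comparison outright could lose much of the second time point.

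The cost is a wording change in Appendix 6, two recorded items per sample, and a tighter booking window that may lose a few samples. No visit is added.
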